### Sample size

Given the novel approach of this study, there is little comparable research available to use for a sample size calculation. We are also somewhat restricted by the number of potential patients available within a given time period in the dental practice. However, we do have data from our own pilot work in a simulated dental setting, which we have used to make an informed estimate of the required sample size for the current study.

The sample size calculation (with a power of 0.80, significance level of 0.05 and based on 2-sided testing) is based on one of the main outcomes related to memories, ‘intrusive thoughts’, as measured with an 11-point verbal rating scale. In our pilot study, the standard deviation for this outcome in our control group was 1.25 and we have conservatively used an estimated standard deviation of 1.3 in this sample size calculation. Based on these assumptions, and comparing the two VR groups against the control group, following up a total sample size of 90 patients (that is, 30 per group) would allow the detection of a between-group difference of around 0.82 units (that is, a moderate effect size). Since drop-outs are unavoidable when collecting follow-up data, this number needs to be adjusted for the estimated drop-out rate. In our simulation study, we had a drop-out rate of 10% for collecting the follow-up data, but since we paid participants for participation in that study (although they received their pay after the simulated treatment and before participating in the follow-up interview), we anticipate a higher drop-out rate for this study, and have allowed for a 15% drop-out rate. Adjusting the sample size for this drop-out rate results in a sample of 108 patients needing to be recruited.

The use of technical computer equipment is associated with the risk of technical failures. In the pilot study we had to exclude 6 of 75 participants because the VR crashed or the remote stopped working during the simulated treatment and the participant was no longer able to interact with the VR environment. Several improvements in the VR program have been made since, such as putting force fields in place that restrict the area of virtual exploration, but we still anticipate the exclusion of participants because of technical issues. We will therefore increase the sample size by a further 8%, resulting in a total recruitment target of 120 for this study (that is, 40 patients per group).

### Procedure

This study will include both referred patients and in-house patients from a dental clinic in the United Kingdom. Since there are some differences in the timing and scheduling of contacts between the practice and the two types of patient, two separate procedures are described.

#### *Referral patients*

Referral patients will receive a letter from the practice about their appointment date in the post. The patient information leaflet about the study will be included. On average, this is about 12 weeks before the treatment takes place.

When the patient comes in for a preoperative assessment, informed consent will be obtained, at the end of this appointment. On average, this is 4 weeks before the treatment appointment. After obtaining informed consent, and at the end of the preoperative assessment appointment, the dentist or nurse will hand a baseline questionnaire to the patient. The patient will be asked to complete these questions at the practice before going home. Patients will be asked to complete a dental anxiety questionnaire, reporting their oral health status and anticipated pain. Completing the questionnaire will take between 5 and 10 minutes.

#### *In-house patients*

In-house patients will have routine check-up appointments at the practice and, if they need treatment, they will be booked in for a treatment appointment. At this point, they will receive the patient information leaflet and will be asked for their informed consent. Owing to the way the healthcare process is organized in the practice, a cooling-off period at this time for the in-house patients cannot be provided. However, at this stage of the study, they will only be asked to complete a baseline questionnaire. Patients will be asked to confirm their consent when they attend their treatment appointment, which is on average 25 days later. This allows the patient to think about their participation in the trial and ask any questions they might have.

After obtaining informed consent, and at the end of the appointment, the dentist or nurse will hand a baseline questionnaire to the patient. The patient will be asked to complete these questions at the practice before going home. Patients will be asked to complete a dental anxiety questionnaire, reporting their oral health status and anticipated pain. Completing the questionnaire will take between 5 and 10 minutes.

#### *For both patient groups*

Patients will be randomized when they attend their scheduled treatment appointment (that is, after baseline data has been recorded). If a patient decides that he or she no longer wants to participate in the study, the baseline data will be discarded. When undergoing their scheduled dental treatment, patients will be exposed to either one of the VR conditions (natural or urban VR environment) or the control condition (usual care). Standard clinical procedures will be followed and when treatment will be started, patients will either be handed a pair of VR goggles (when assigned to the VR groups) or a pair of protective glasses (when assigned to the standard care group). Patients in the VR groups will receive an explanation of how to use the controller by a member of staff. Heart rate will be monitored during dental treatment by a staff member using a pulse oximeter on a finger of the hand that is not operating the controller. The output of the pulse oximeter throughout the treatment session will be recorded by the dentist or nurse. After treatment, staff will record the treatment characteristics and patient characteristics. The patient will be asked to complete a questionnaire in the waiting room before leaving the dental practice. This questionnaire takes about 10 minutes to complete and consists of four parts; treatment experience, VR experience, dental experience and demographic information. The patient will be provided with an envelope, in which to seal the questionnaire.

One week after treatment, patients will receive a phone call, during which we will ask them about their memories and dental anxiety. This phone call will be made by one of the members of the research team and will take between 5 and 10 minutes. After responding to the questions, patients will be debriefed and will be asked if they would like to receive the results of the study. If patients ask questions regarding their clinical care during this interview, it will be tactfully explained to them that the interviewer is not a clinician and they will be directed to the practice for a response to any such queries.

### Outcome measures

#### *Main study parameters*

We developed a questionnaire that assessed intrusive thoughts of the experience and vividness of memories of the experience. This questionnaire is based on the Alcohol Craving Experience Questionnaire [35]. This was developed to assess craving based on the elaborated intrusion theory and measures vividness of memories and intrusive thoughts. The questions to measure memories and intrusive thoughts were used in our pilot work and showed sufficient reliability in that study (Cronbach’s alpha of respectively 0.69 and 0.81). They are slightly adapted to fit the purposes of the current study.

• Vividness of memories will be measured with five items on an 11-point verbal rating scale (VRS).

• Intrusive thoughts about the experience will be measured with three items on an 11-point VRS.

• Remembered pain will be measured with an 11-point VRS [36].

• Patients will respond to an open-ended question about the three things they remember most and to indicate, for each of these three things, how pleasant or unpleasant their thoughts were. They will also be asked how well they remember what the dentist said.

#### Secondary study parameters

The patient will complete questionnaires after their preoperative assessment, immediately after their treatment and 1 week after their treatment (phone call). Table 1 gives an overview of the measures, and at which time points they will be completed. The following parameters will be measured:

**Table 1 T1:** Overview and timing of measurements

**Measures**	**Times**				**Completed by**	**Using**	**Where**
	**After preoperative assessment**	**During treatment**	**After treatment**	**Follow-up**			
**Dental anxiety**	X (T1)		X (T2)	X (T3)	Patient	Questionnaire after preoperative assessment (T1)	At the practice (waiting room) (T1 and T2)
						Questionnaire for the patient after treatment (T2)	Via phone (T3)
						Follow-up questionnaire (T3)	
**Treatment characteristics**			X		Staff	Data recording sheet for staff	At the practice
**Patient characteristics**			X		Staff	Data recording sheet for staff	At the practice
**Self-reported oral health status**	X				Patient	Questionnaire after preoperative assessment	At the practice (waiting room)
**Anticipated pain and anxiety**	X				Patient	Questionnaire after preoperative assessment	At the practice (waiting room)
**Demographics**			X		Patient	Questionnaire for the patient after treatment	At the practice (waiting room)
**Previous cancellations**			X				
**Treatment experience**			X		Patient	Questionnaire for the patient after treatment	At the practice (waiting room)
**Stress (physiological)**		X			Staff	Pulse oximeter	In treatment area
**Virtual reality experience**			X		Patient	Questionnaire for the patient after treatment	At the practice (waiting room)
**Dental experience**			X		Patient	Questionnaire for the patient after treatment	At the practice (waiting room)
**Memories (follow-up)**				X	Patient	Follow-up questionnaire	Via phone

##### Treatment experience

• Pain will be measured with an 11-point VRS [36].

• Discomfort will be measured with two questions on an 11-point VRS [25].

• Stress will be measured with a self-reported measure and a physiological indicator (heart rate). The self-reported measure consists of five items from the tension dimension from the Profile of Mood States [37]. Heart rate will be monitored using a pulse oximeter and the output will be recorded.

• Time perception will be measured with one question in which patients are asked to estimate how many minutes they think they have been wearing the VR goggles or protective glasses [38].

• Perceived control will be measured with an 11-point VRS.

##### Dental experience

• To measure communication with the dentist, patients will be asked to indicate on an 11-point VRS how much attention they paid to what the dentist said.

• Revisit intentions and likeliness of avoidance will be measured by asking participants how much they would like to avoid similar treatment in the future.

• Dental anxiety will be measured immediately after treatment and a week later at follow-up, using the Modified Dental Anxiety Scale (MDAS), which consists of five items [39].

• Treatment satisfaction will be measured with six statements, on an 11-point VRS, about participants’ last visit to a dental practice, based on the Service Quality (SERVQUAL) questionnaire [40].

##### 

**VR experience** The questions about the VR experience will only be asked to patients in the two VR groups.

• Presence will be measured with six items on 11-point verbal rating scales, based on the IGroup Presence Questionnaire [41] and the Reality Judgment and Presence Questionnaire [42].

• Perceived restoration will be measured with eight items on a 5-point scale [43].

• Attractiveness will be measured with five items on a 5-point bipolar adjective scale [19].

• Awareness of the surrounding dental environment will be measured with one question on an 11-point VRS.

• Nausea will be measured with an 11-point VRS [25].

• Intention to use VR goggles again will be measured with an 11-point VRS.

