#### *Additional predictions*

##### 

**Treatment experience** Compared with standard care, VR exposure (in general) will lead to less self-reported: (1) pain, (2) discomfort and (3) stress. It will also lead to (4) a lower average heart rate (an index of physiological stress) and (5) an underestimation of time elapsed (reflecting the ability of the VR environment to engage patients). For all of these outcomes, we further predicted that the natural VR environment will produce more positive outcomes than the urban VR environment. Additionally, we predict that (6) the use of VR will lead to more perceived control.

##### 

**Dental experience** Patients exposed to VR environments will show (7) lower subsequent levels of dental anxiety than those exposed to standard care and (8) improved intentions to revisit the surgery. Again we hypothesized that these effects would be greater in the natural than in the urban VR.

##### 

**Virtual reality experience** The natural VR environment will be perceived as more (9) attractive and (10) psychologically restorative than the urban environment. Moreover, (11) VR exposure will lead to a reduced awareness of the surrounding environment.

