### Data analysis

The data will be recorded and analyzed using SPSS 20.0. All data will be analyzed using an intention-to-treat analysis. Descriptive statistics will be calculated. Discrete variables will be summarized by frequencies or proportions. Continuous variables will be reported as means and standard errors or medians and range (depending on the distribution of the variables). Data will be checked for baseline differences between the treatment arms. If baseline differences do occur for any of the variables, they will be added to subsequent models to compensate for those differences using an analysis of covariance approach.

Analyses of covariance (ANCOVAs) will be performed for each of the outcome measures with VR condition (that is, natural, urban or control) as the independent variable and baseline dental anxiety as the covariate, including planned contrasts to explore specific hypotheses. Contrasts for VR condition will be based on comparisons of VR (both natural and urban environments combined) with the no VR control group (comparison 1), natural VR with urban VR (comparison 2), natural VR with the control group and urban VR with the control group (Table 2 gives an overview of specific predictions being tested).

**Table 2 T2:** Overview of the specific comparisons for each prediction

	**Prediction**	**Comparison 1:**	**Comparison 2:**	**Comparison 3:**
		**virtual reality (both natural and urban environments) vs no virtual reality (control group)**	**natural virtual reality vs urban virtual reality**	**(a) natural virtual reality vs control**

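### Prediction 11 is to be tested as VR versus control, but the awareness question is placed in a block that control patients are not asked

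*Protocol article*

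**What the plan says.** Three places in the protocol article bear on this point.

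- **Additional predictions, Virtual reality experience.** Prediction 11 reads: "VR exposure will lead to a reduced awareness of the surrounding environment". Predictions 9 and 10, in the same paragraph, are worded as natural against urban; prediction 11 is worded as an effect of VR as such.
- **Data analysis and Table 2.** The planned contrasts include "comparisons of VR (both natural and urban environments combined) with the no VR control group (comparison 1"). In Table 2, prediction 11 has one tick, under comparison 1. It has none under natural versus urban, and none under either VR group separately against control.
- **Outcome measures, VR experience.** The block opens with "The questions about the VR experience will only be asked to patients in the two VR groups". Among the items listed beneath that sentence is: "Awareness of the surrounding dental environment will be measured with one question on an 11-point VRS".

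Table 1 shows the VR experience measures as a single row, completed by the patient in the waiting room after treatment, with no separate entry for awareness.

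**The concern.** The analysis section names the control group as comparator for an outcome that the measurement section withholds from that group. The two statements cannot both be carried out. This is not a detail left for an analysis plan to settle, because no analysis can supply control scores that were not collected.

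The stake is modest but real. The Background gives the shutting out of the treatment surroundings as one reason why goggles may work better than other distractions. Prediction 11 is the only listed prediction that examines this directly. Without control scores the trial could describe how aware VR patients felt, but could not say that VR had lowered awareness.

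**Working it through.** **1. The plan's own figures.** The Sample size section works "with a power of 0.80, significance level of 0.05 and based on 2-sided testing", and states that "we have conservatively used an estimated standard deviation of 1.3 in this sample size calculation". Its comparison is "comparing the two VR groups against the control group, following up a total sample size of 90 patients (that is, 30 per group"), which "would allow the detection of a between-group difference of around 0.82 units". With 60 VR and 30 control patients:

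- Detectable difference = (1.960 + 0.842) × 1.3 × √(1/60 + 1/30) = 2.802 × 1.3 × 0.2236 = 0.81 (normal approximation). The t-test version gives 0.82.
- Power at a difference of 0.82 is 0.805 (normal approximation).
- Drop-out of 15%: 30 / 0.85 = 35.3, rounded up to 36 per group, or 108 in all.
- Technical failures of 8%: 36 / 0.92 = 39.1, rounded up to 40 per group, or 120 in all.

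The stated sample size therefore reproduces. It was set on intrusive thoughts and does not depend on the awareness item.

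**2. Measurement against planned comparison.** The three predictions in the VR experience paragraph are set side by side:

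| Prediction | Outcome | Comparison in Table 2 | Groups needed | Groups asked |
|---|---|---|---|---|
| 9 | Attractiveness | 2 | Natural, urban | Natural, urban |
| 10 | Restoration | 2 | Natural, urban | Natural, urban |
| 11 | Awareness | 1 | Natural, urban, control | Natural, urban |

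Predictions 9 and 10 are consistent. Only prediction 11 needs a group that is not asked. With zero control scores, the term 1/n for the control group is undefined and the contrast has no estimate.

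**3. Is there a control measure elsewhere?** The nearest item is how closely patients attended to the dentist's words. The article labels it a measure of communication, not awareness of the surroundings. Presence sits in the same VR-only block. No other item serves.

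**4. What the comparison would have if all groups were asked.** The item is completed straight after treatment, so the loss expected at the one-week phone call does not apply. The upper limit is the number recruited, 80 VR and 40 control, before technical exclusions. The article gives no standard deviation for awareness, so precision can be shown only in SD units (80% power, two-sided 0.05, normal approximation, no covariate adjustment):

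- 80 versus 40: standard error √(1/80 + 1/40) = 0.194 SD; detectable difference 2.802 × 0.194 = 0.54 SD.
- 60 versus 30, the number planned at one week: standard error 0.224 SD; detectable difference 0.63 SD.

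The second line is a cautious lower case, not the expected number for this outcome.

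**The case against.** The strongest reply is that this may be a drafting slip. The article condenses a fuller protocol and does not reproduce the questionnaire. The item may simply be filed under the wrong heading, or the restricting sentence may be broader than intended. That stands as a limit: a reader might infer that controls are in fact not being asked, and the article cannot establish this. It establishes only that its measurement and analysis sections conflict and must be reconciled.

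A second reply is that little depends on the item. This also stands. Prediction 11 is the last of eleven additional predictions and rests on one question among the secondary parameters. The primary outcomes are remembered pain, intrusive thoughts and vividness at one week. None of these, nor the three overall hypotheses, uses the awareness score. A reader might take the conflict for a flaw that undermines the trial; the documents do not support that.

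A third reply is that missed control answers are not wholly lost, since every patient is to be telephoned a week later about memories of treatment. That is fair, so it would be too strong to call the data irrecoverable. But a recollection at one week is a weaker measure than an answer in the waiting room, and it would differ in timing from the VR groups' scores.

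It could also be said that Table 2 was damaged when the text was extracted. The tick pattern argues against this: rows 9 and 10 have an empty first column, while row 11 has its tick there, as row 6 does. The wording of prediction 11 itself also implies a no-VR reference.

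**Conclusion.** The point holds. As the article is written, prediction 11 has a planned VR-versus-control test and no control data, so the test cannot be carried out. The loss is complete for that one comparison (0 of 40 planned controls) and nil for the primary outcomes, the sample size and predictions 9 and 10. It should be fixed, but it is not critical to the trial.

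The conclusion rests on reading the restriction to the VR groups as covering every item listed beneath it, which is its plain meaning. The figure of 80 versus 40 assumes full recruitment and a completed questionnaire from every patient, before technical exclusions; the detectable differences in SD units are illustrative.

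**What to change.** Move the awareness question to the part of the post-treatment questionnaire answered by all three groups, and leave Table 2 as it is. Check that the wording makes sense for patients in protective glasses. The time-perception item under Treatment experience already refers to either kind of eyewear and can serve as the pattern.

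If the item must stay in the VR-only block, withdraw the VR-versus-control test of prediction 11, delete its tick in Table 2, and report awareness descriptively within the VR groups. Moving the tick to comparison 2 would not rescue the prediction: natural against urban is a different hypothesis, which the article does not state for awareness.

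The cost is one further question for control patients, possibly some rewording, and a minor amendment. At submission only two patients had been randomized (Trial status), so a prompt correction would have preserved nearly all the control data.

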#### *Inclusion criteria*

1. All patients who are scheduled to undergo dental treatment for fillings or extractions with a planned maximum treatment length of 30 minutes are eligible to participate in the study.

2. This includes both referred patients and in-house patients.

3. Both patients who need relative analgesia (RA) and patients who are treated without sedation will be included.

4. Patients 18 years or older will be included.

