#### *Exclusion criteria*

1. Patients who need intravenous sedation cannot participate in the study.

2. Patients who have previously had epileptic seizures cannot participate in the study, owing to the very small risk that an episode can be triggered by using the HMD, similar to the episodes that might be triggered by watching television.

3. If a patient is scheduled for more than one treatment during the trial period, the patient will only be included for the first treatment.

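### Nausea is asked only in the two VR groups, so the trial will have no randomised VR-versus-control estimate of it; awareness of the surroundings has the same gap

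*Protocol article*

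**What the plan says.** In the protocol article, Secondary study parameters, the VR experience block covers presence, perceived restoration, attractiveness, awareness of the dental surroundings, nausea and willingness to use the goggles again. The nausea entry reads "Nausea will be measured with an 11-point VRS". The block opens with a restriction: "The questions about the VR experience will only be asked to patients in the two VR groups".

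The block belongs to a questionnaire filled in at the practice straight after treatment, which "consists of four parts; treatment experience, VR experience, dental experience and demographic information". Controls complete that questionnaire apart from the VR block. One item in the treatment experience part is already worded for every arm; it asks "how many minutes they think they have been wearing the VR goggles or protective glasses".

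On eligibility the article says: "Both patients who need relative analgesia (RA) and patients who are treated without sedation will be included". Sedation (relative analgesia, yes or no) is a randomisation stratum.

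Data analysis plans ANCOVAs "for each of the outcome measures with VR condition (that is, natural, urban or control) as the independent variable". Comparison 1 in Table 2 is both VR groups together against control. Nausea has no row in Table 2. Prediction 11, reduced awareness of the surroundings under VR, has a tick under Comparison 1 only.

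**The concern.** Most items in the block are judgements about the virtual environment or the equipment, and a control patient cannot answer them. Nausea is a symptom. All arms have fillings or extractions, and patients in any arm may have relative analgesia, so some nausea without VR is plausible. The article gives no figure for it, and the design will not supply one.

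The resulting nausea score among VR users could be misread in either direction: background nausea put down to the goggles, or a real VR effect dismissed as background. A later analysis plan cannot repair this, because the control values will not have been collected.

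Nausea is also the only side effect of the VR type that the article lists as a measured item. The other VR-related risk it names, seizure, is dealt with by exclusion ("owing to the very small risk that an episode can be triggered by using the HMD") and is not listed as an outcome.

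**Working it through.** **1. What can be estimated as planned.** Set the VR experience restriction beside the analysis plan:

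| Item | Asked of controls? | Comparison in Table 2 | Can it be run? |
|---|---|---|---|
| Nausea | No | None listed; the general ANCOVA sentence includes control as a level | Natural v urban only |
| Awareness of surroundings | No | Comparison 1 (VR v control), prediction 11 | No |
| Pain, discomfort, stress | Yes | Comparisons 1, 2 and 3 | Yes |

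With no control observations, the three-level model cannot be fitted for nausea, and the only comparison listed for prediction 11 has no control data.

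**2. The plan's own sample size, as a check on the inputs.** From Sample size: SD 1.3, power 0.80, two-sided 0.05, 60 VR v 30 control.
- Detectable difference = (1.960 + 0.842) × 1.3 × √(1/60 + 1/30) = 2.802 × 1.3 × 0.2236 = 0.81. The article says around 0.82.
- Drop-out of 15%: 30/0.85 = 35.3, rounded up to 36 per group, 108 in total.
- Technical failure of 8%: 36/0.92 = 39.1, rounded up to 40 per group, 120 in total.

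All the stated figures reproduce, and nothing in this point changes them.

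**3. What asking every arm about nausea would give.** The article has no SD for nausea, so the results are in SD units. The 95% half-width is 1.96 × √(1/n_VR + 1/n_control); the detectable difference at 80% power replaces 1.96 with 2.802.
- 80 v 40: √(1/80 + 1/40) = 0.1936. Half-width 0.38 SD; detectable 0.54 SD.
- 60 v 30: √(1/60 + 1/30) = 0.2236. Half-width 0.44 SD; detectable 0.63 SD.

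The item is answered before patients leave the practice, so the allowance for losses at the one-week call need not apply. The 60 v 30 line is the pessimistic case.

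In points, using the t multiplier 1.98 for 80 v 40 and **assumed** SDs of 1.5, 2.0 and 2.5 on the 11-point scale, the half-widths are 0.58, 0.77 and 0.96.

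**4. What the planned design offers instead.** Natural v urban at 40 v 40 has a detectable difference of 2.802 × √(2/40) = 0.63 SD. It compares two kinds of VR content and says nothing about VR against no VR.

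**The case against.** The strongest reply is that nausea carries no claim. It is in none of the three overall hypotheses, none of the eleven additional predictions and no row of Table 2. It can be read as a description of VR users' experience, and the general sentence about ANCOVAs for every outcome also fails for items such as presence, so that sentence is loosely written and does not show a specific error over nausea. This stands, and it keeps the point minor. It does not create a VR-versus-control estimate.

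A second reply is that the wording of the item is not shown. If it asks about nausea caused by the goggles, it cannot be given to controls unchanged. That also stands, and the fix must include neutral wording.

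The documents do not support four stronger readings that a reader might infer:
- **Nausea is the only harm the trial records.** The article is condensed, and adverse-event recording may sit in the full protocol.
- **Nausea is the only item in the block that controls could answer.** Awareness of the surroundings can also be asked of them, and it is the item for which Table 2 does plan a comparison with control.
- **Conclusions about the overall experience are weakened.** Pain, discomfort, stress, perceived control, avoidance, dental anxiety and satisfaction are not in the VR-only block.
- **Nausea could usefully be estimated within sedation strata.** The article gives no number of patients with relative analgesia. If a quarter had it (an assumption), 20 v 10 would give a half-width of 1.96 × √(1/20 + 1/10) = 0.76 SD, which is too wide to help.

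**Conclusion.** The point holds as a minor design weakness. As written, the trial yields no randomised VR-versus-control estimate of nausea, only natural versus urban, and so cannot tell VR-related nausea from background nausea. Asking all arms would give a 95% half-width of about 0.38 SD with 80 v 40, or 0.44 SD with 60 v 30. These figures assume approximately normal means and equal variances; any version in points rests on an assumed SD.

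The same restriction contradicts Table 2 for prediction 11, where a comparison with control is planned on an item that controls are not asked. The primary outcomes and the sample size are untouched. That background nausea is appreciable is plausible, but the article does not show it.

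**What to change.** Move the nausea item to the treatment experience part that all three groups complete, worded neutrally as nausea during treatment. Report Comparison 1 for nausea with a 95% confidence interval, adjusted for the sedation stratum, as a secondary tolerability outcome. Ask the awareness item of all arms as well, so that the comparison planned for prediction 11 can be run. Leave the remaining VR experience items with the two VR groups.

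The cost is one or two extra 11-point items on a questionnaire that controls already fill in, together with whatever approval a changed questionnaire needs. Two patients had been randomised when the article was submitted, so a change at that stage would have lost almost no data. Recruitment stays at 120.
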